# PReoperative very low-Energy diets for obese PAtients undergoing non-bariatric surgery Randomized Evaluation (PREPARE): a protocol for a pilot randomized controlled trial

**DOI:** 10.1186/s40814-024-01511-6

**Published:** 2024-05-21

**Keywords:** Surgical procedures, Obesity, Weight loss, Weight loss products, Preoperative optimization, Prehabilitation

## Abstract

**Background:**

Patients with obesity presenting in need of surgical intervention are at 2-to-sixfold higher risk of prolonged hospitalization, infectious morbidity, venous thromboembolism, and more. To mitigate some of these concerns, prescribed preoperative weight loss via very low-energy diets (VLEDs) has become a standard of care for patients with obesity undergoing bariatric surgery. While VLEDs have become standard prior to bariatric surgery, their application in other surgical settings remains limited. A large, definitive trial is required to resolve the uncertainty surrounding their use in these patients. Prior to a definitive trial to compare the efficacy of VLEDs in patients with obesity undergoing major non-bariatric surgery, we require a pilot trial. We argue a pilot trial will provide the following critical feasibility insights: (1) assessment of recruitment ability, (2) evaluation of adherence to VLED regimens, and (3) assessment of our ability follow patients completely.

**Methods:**

The proposed trial will be a multi-center, surgeon, outcome assessor, and data-analyst blinded, parallel pilot randomized controlled trial (RCT). Patients older than 18 years of age with a body mass index (BMI) of greater than 30 kg/m^2^ undergoing major elective non-bariatric surgery will be eligible for inclusion. Consecutive patients will be allocated 1:1 according to a computer-generated randomization schedule. Randomization will be stratified by center and will employ randomly permutated blocks. All patients in the intervention group will receive standard patient counseling on weight loss and an active VLED protocol. The preoperative VLED protocol will utilize commercially available weight loss products for three weeks preoperatively. The primary outcomes (randomization percentage, recruitment rate, intervention adherence, follow-up completion, network development) will assess feasibility. Descriptive statistics will be used to characterize the study sample.

**Discussion:**

The PREPARE pilot RCT will aim to provide feasibility and safety data that will allow for the successful completion of the definitive PREPARE trial that has the potential to provide practice changing data pertaining to the regular use of VLEDs as a means of pre-habilitation for patients with obesity undergoing major non-bariatric surgery.

**Trial registration:**

This study was registered on ClinicalTrials.gov (reference #NCT05918471) on June 23, 2023.

**Supplementary Information:**

The online version contains supplementary material available at 10.1186/s40814-024-01511-6.

## Introduction

Obesity is a worldwide epidemic affecting upwards of 700 million people [1]. The economic burden in the United States and Canada are estimated at over $2 trillion and $100 billion United States dollars (USD), respectively, and the resultant healthcare consequences can be devastating for systems and patients alike [2]. Obesity is a systemic disease with significant consequences for patients undergoing any form of medical or surgical intervention [3, 4]. Patients with obesity presenting in need of medical and surgical intervention are at 2-to-sixfold higher risk of prolonged hospitalization, infectious morbidity, venous thromboembolism, and more [5–8]. In the postoperative period in particular, their risk of morbidity is significantly increased. Incidence of cardiovascular (1–2% vs. 2–4%), genitourinary (3–10% vs. 6–20%), and wound (3-–9% vs. 6–18%) complications are at least doubled compared with patients without obesity [9–13]. These worsened short-term postoperative outcomes not only prolong recovery following surgery, but they also result in significantly longer length of stay and greater healthcare spending [14, 15].

To pre-emptively mitigate some of these concerns, prescribed preoperative weight loss via very low-energy diets (VLEDs) has become a standard of care for patients with obesity undergoing bariatric surgery (i.e., weight loss surgery) [16]. This type of surgery typically involves restricting oral intake or bypassing parts of the gastrointestinal tract to limit macronutrient absorption to help patients lose weight. The Canadian Adult Obesity Clinical Practice Guidelines and Enhanced Recovery After Surgery (ERAS) guidelines recommend 2–3 weeks of preoperative VLED with liquid formulations prior to bariatric surgery [16, 17]. These programs can effectively induce significant amounts of preoperative weight loss [18–20]. This contributes to decreased postoperative length of stay (LOS) by 0.5–1 days and decreased fat content by as much as 29% around the major organs resulting in better visualization and improved ease of the surgery [20–23]. The impact on postoperative morbidity, however, is less clear. We performed a systematic review and meta-analysis of four small RCTs (sample sizes 20 to 273) evaluating VLEDs in obese patients undergoing bariatric surgery demonstrating a 33% reduction in the risk of major complications with VLED—a point estimate suggesting an important benefit; however, the wide 95% confidence intervals (CIs) and resultant type II error risk create significant uncertainty (RR 0.67, 95% CI 0.39–1.17, *p* = 0.16, *I*^2^ = 0%) [18].

While VLEDs have become a standard in patients with obesity undergoing bariatric surgery, largely due to the significant reduction of peri-organ fat for better visualization, their application to obese patients undergoing other types of surgery remains limited [24]. We performed a systematic review and meta-analysis that identified 13 studies evaluating the use of preoperative VLEDs in patients with obesity undergoing orthopedic, vascular, colorectal, upper gastrointestinal, gynecological, and a variety of general surgery procedures for benign disease (e.g., cholecystectomy, abdominal wall hernia) [24]. While data were heterogenous, preoperative VLEDs reliably resulted in significant weight loss (3.2–19.2 kg) with high rates of adherence to the protocols (94–100%). Adverse event rates were low (< 14% in most studies). There were no significant differences in postoperative outcomes, though again pooled analyses included a small number of patients and there were wide corresponding 95% CIs. We have also shown that other forms of preoperative weight loss, such as bariatric surgery, prior to major abdominal surgery can improve postoperative outcomes [25]. Specifically, weight loss induced by bariatric surgery prior to surgery for colorectal cancer can contribute to a 25% relative risk reduction in overall postoperative morbidity, 43% relative risk reduction in gastrointestinal morbidity, and 47% relative risk reduction in respiratory morbidity [25]. Preoperative weight loss by way of preoperative VLEDs has the potential to do the same [20]. The evidence for routine use of VLEDs in patients with obesity undergoing major non-bariatric surgery is compromised by heterogeneous, small studies with methodological limitations. A large, definitive trial is required to resolve this uncertainty. Prior to a definitive trial to compare the efficacy of VLEDs in patients with obesity undergoing major non-bariatric surgery, we require a pilot RCT. We argue a pilot trial will provide the following critical feasibility insights: (1) assessment of recruitment ability, (2) evaluation of adherence to VLED regimens, and (3) assessment of our ability follow patients completely.

## Materials and methods

### Pilot trial objectives

The objective of this pilot RCT is to determine the feasibility of a multicenter RCT comparing patients with obesity (i.e., BMI > 30 kg/m^2^) receiving VLEDs versus control prior to elective non-bariatric surgery in terms of perioperative outcomes. The specific feasibility objectives of this trial are as follows: (1) determine the feasibility of recruiting patients in a timely manner across local and outside sites; (2) determine adherence with preoperative VLEDs in patients with obesity undergoing elective non-bariatric surgery; (3) determine the feasibility of completion of follow-up; (4) determine our ability to develop a network of participating sites in a multi-site initiative; (5) determine the safety of administering preoperative VLEDs to patients with obesity undergoing elective non-bariatric surgery. We postulate this pilot RCT will demonstrate feasibility and thus offer support for a full RCT aimed at evaluating the efficacy of preoperative VLEDs in patients undergoing major non-bariatric surgery in terms of perioperative outcomes.

### Trial design

The proposed trial will be a multi-center, surgeon, outcome assessor, and data-analyst blinded, parallel pilot RCT. The trial will be reported according to the Consolidated Standards of Reporting Trials (CONSORT) Extension for Randomized Pilot and Feasibility Trials [26].

### Study centers

This pilot trial will include 4 centers: (1) St. Joseph’s Healthcare Hamilton (local); (2) Juravinski Hospital, Hamilton (local); (3) Hamilton General Hospital (local); (4) Kingston Health Sciences (outside site). Throughout the pilot RCT, we will be seeking active engagement from at least 6 other centers to have at least 10 centers involved in the full RCT.

### Trial population

The inclusion criteria are as follows: (1) older than 18 years of age, (2) BMI of greater than 30 kg/m^2^, (3) undergoing major elective non-bariatric surgery*.* Major surgery is defined as any thoracic, abdominal, cardiovascular, orthopedic, oncologic, or reconstructive operation performed under general anesthesia requiring a skin incision extending beyond the subcutaneous tissue.

The exclusion criteria are as follows: (1) undergoing bariatric surgery; (2) undergoing neurologic surgery; (3) undergoing urgent or emergent surgery; (4) recently diagnosed myocardial infarction or unstable angina (i.e., within past 6 months); (5) diagnosed moderate-to-severe renal dysfunction (i.e., eGFR less than 30 mL/min/1.73 m^2^); (6) diagnosed severe liver dysfunction (i.e., cirrhosis, portal hypertension, hepatic encephalopathy, hepatorenal syndrome); (7) recently diagnosed alcohol or drug use disorders (i.e., excessive use of substance within past 6 months); (8) recently diagnosed, uncontrolled eating disorder (e.g., bulimia nervosa, binge eating disorder within the past 12 months); (9) recent episode of gout (i.e., within past 6 months); (10) history of porphyria; (11) known allergy to any Optifast® or Medimeal® ingredient; (12) enrolled in other prospective studies with similar interventions and/or outcomes; co-enrollment may be deemed appropriate if the steering committees of the respective trials review the details of participation and determine the likelihood of interaction between interventions is low; (13) pregnant or breastfeeding women; (14) patients residing in a long-term care facility; (15) patients unable to provide informed consent.

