### Recruitment

Patient recruitment will occur at Hamilton Health Sciences (i.e., Juravinski Hospital, Hamilton and Hamilton General Hospital), St. Joseph’s Healthcare Hamilton, and Kingston Health Sciences. All surgeons who perform elective non-bariatric surgery at these sites will be made aware of the study via workshops and internal communications. Patients will be identified by the surgeons, their administrative assistants, patient navigators, and/or study investigators at the time of referral or at the time of their initial preoperative consultation. Surgeons and/or other clinicians within a patient’s circle of care will introduce the study to participants at the time of their preoperative visits. Patients meeting inclusion criteria based on a review of their electronic medical record will be approached by designated research personnel at the time of their initial surgical consultation in clinic. If the patient is not identified in time, or if it is not feasible for the research personnel to approach the patient in person at the time of their consultation, the patient will be contacted by telephone within one-week of their consultation. At the time of initial contact between the study personnel and patient, the study will be introduced, and eligibility will be confirmed. Once eligibility is confirmed, the written informed consent process will ensue. After documentation of written informed consent, patients will be registered using a web-based randomization system. Consecutive patients will be allocated 1:1 according to a computer-generated randomization schedule to one of the two treatment arms. Randomization will be stratified by center and will employ randomly permutated blocks.

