### Planned trial interventions

#### Intervention group (VLED protocol plus counseling)

All patients in the intervention group will receive patient counseling on weight loss and an active VLED protocol. The preoperative VLED protocol will utilize commercially available weight loss products, such as Optifast® 900, Medimeal®, or a similar product. Patients will receive a 3-week supply. They will start taking the VLED 3 weeks and 2 days prior to their surgery date (i.e., 23 days prior to their surgery date) and finish the intervention the evening of their second last day prior to surgery. This timeframe was chosen to not interfere with any other perioperative intervention required for a given surgery (e.g., bowel preparation, carbohydrate loading). They will be instructed to consume four packets daily. This provides a total energy intake of 900 kcal. Patients will also be able to consume up to 2 cups of low-calorie vegetables per day along with the meal replacement product. They will be provided with a handout containing specific instructions. Patients will keep self-report diaries of their dietary intake and activity levels. Patients enrolled in the trial and assigned to the VLED group who are diabetics will be referred to a diabetes educator nurse practitioner for management of their insulin dosing and/or other anti-hyperglycemic medications throughout the duration of the intervention period.

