The current protocol in use at our local Bariatric Surgery Center utilizes four doses commercially available VLED daily and the duration varies between 1 and 3 weeks based on liver size and BMI. We have adapted this for the purposes of the present trial as presented in Additional file 1. To standardize the approach for non-bariatric surgery, we propose an intervention period of 3 weeks. In our systematic review of preoperative VLEDs prior to non-bariatric surgery, 95% CIs for weight loss resulting from programs lasting between 3 and 8 weeks overlapped significantly [24]. This plateau coupled with time constraints for the preoperative waiting period for certain patient populations (e.g., cancer patients), served as reasoning for our 3-week intervention period. Our systematic review identified protocols varying from 0.46 to 26 weeks that were safe and efficacious, and thus we are confident that our intervention period is appropriate [24]. In our systematic review and meta-analysis, Optifast® was the most commonly studied VLED liquid formulation (35.7% of included studies) and daily target caloric intake ranged from 450 to 1400 kcal per day [24].

Adherence to a preoperative 2-to-3-week regimen of preoperative VLED prior to bariatric surgery ranges from 80 to 90% [27, 28]. In our systematic review and meta-analysis evaluating the use of VLEDs in non-bariatric surgery, reported adherence ranged from 94 to 100% among the included studies, with much longer durations of intervention (0.46–24 weeks) [24]. We anticipate adherence in this study will be similar and range between 80 and 100%. To increase adherence with the study medication, we will cover the cost of the VLED and have patients complete a diet diary.

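### The eligibility and recruitment sections omit the timing window that the diet schedule and Table 1 require, which leaves two primary feasibility outcomes ambiguous

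*Protocol article*

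**What the plan says.** Trial population lists three inclusion criteria, "1) older than 18 years of age, (2) BMI of greater than 30 kg/m^2^, (3) undergoing major elective non-bariatric surgery", and 15 exclusions. The exclusion closest to timing is "3) undergoing urgent or emergent surgery", which removes unplanned surgery but sets no interval for elective cases.

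Recruitment has research staff approach patients who meet the inclusion criteria on record review, at the initial surgical consultation. Failing that, "the patient will be contacted by telephone within one-week of their consultation". Eligibility is confirmed at this first contact, written consent follows, and the patient is then registered in the web-based randomization system. No step refers to the surgery date.

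The intervention section does depend on that date: "They will start taking the VLED 3 weeks and 2 days prior to their surgery date (i.e., 23 days prior to their surgery date"), and patients "finish the intervention the evening of their second last day prior to surgery". Table 1 places eligibility assessment, consent, baseline demographics and baseline anthropometrics only in the day -60 to -23 column, and randomization at day -23.

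Short waits are foreseen. One reason given for a three-week course is "time constraints for the preoperative waiting period for certain patient populations (e.g., cancer patients"), and oncologic operations are within the definition of major surgery.

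**The concern.** The two sets of instructions agree only for patients whose first contact falls 23 to 60 days before surgery. The document does not say what a site should do with anyone else.

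A site that follows Trial population and Recruitment literally will approach and consent elective patients who have too little time for the scheduled course. It will also approach and consent long-wait patients before the Table 1 window opens. A site that follows Table 1 will turn both groups away, although they meet every listed criterion.

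The primary outcome of this pilot is feasibility, and the gap bears on how feasibility is measured:

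- **Randomization percentage** is randomized over approached, with a 70% target. Patients approached at consultation and then found to be out of window may or may not count in the denominator.
- **Dose adherence** is doses taken over doses prescribed, with a mean above 80% as the benchmark. A short lead time can look like non-adherence, or can vanish if the prescription is shortened.
- **Weight-based adherence** compares actual loss with 5% of pre-diet weight. If baseline weight is taken long before the diet starts, the change is not confined to the diet period.

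**Working it through.** **Inputs.** Diet start and end, supply and daily packets come from the intervention section. The -60 to -23 window and the day -23 randomization come from Table 1. The 70% and 80% criteria and their denominators come from Feasibility outcomes. No waiting-time distribution is given anywhere.

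**The plan's calendar.** 3 weeks and 2 days = 3 × 7 + 2 = 23 days, as stated. Day -23 to day -2 inclusive is 23 - 2 + 1 = 22 diet days. With "They will be instructed to consume four packets daily", that is 22 × 4 = 88 packets. But "Patients will receive a 3-week supply", which is 21 × 4 = 84 packets. The two counts need reconciling because they set the adherence denominator, so both are carried below.

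**Short lead.** If first contact is L days before surgery (L < 23) and a truncated diet starts that day, the diet days available are L - 1 (day -L to day -2). The ceiling with perfect compliance is then:

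| L | Diet days | Share of 88 packets | Share of 84 packets |
|---|---|---|---|
| 7 | 6 | 27% | 29% |
| 10 | 9 | 41% | 43% |
| 14 | 13 | 59% | 62% |
| 18 | 17 | 77% | 81% |
| 19 | 18 | 82% | 86% |

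These are ceilings for one patient. They assume that a truncated diet is started and that the denominator stays at the full course; the document settles neither. If the prescription were shortened to fit, the same perfectly compliant 14-day patient would score 100%.

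**Effect on the arm mean (illustrative; shares assumed).** Suppose a fraction f of the diet arm has 14 days' lead and everyone takes 90% of the doses open to them. The mean is 0.90 × [(1 - f) + f × 13/22]. For f = 10% this is 86%, for 20% it is 83% and for 30% it is 79%. The 80% benchmark is crossed only near the top of that range.

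**Effect on the randomization percentage (illustrative; shares assumed).** Suppose a fraction f of those approached is out of window and cannot be randomized, and 80% of the rest agree. The percentage is 0.80 × (1 - f): 72% for f = 10%, 64% for 20%, 56% for 30%. It falls below 70% once f exceeds 1 - 0.70/0.80 = 12.5%. If out-of-window patients are left out of the denominator, it stays at 80%.

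**Long lead.** Within Table 1, baseline weight can precede the diet by at most 60 - 23 = 37 days. A patient whose consultation is 120 days before surgery, if measured then, has a baseline 120 - 23 = 97 days before the diet. Recruitment does not say that baseline is measured at first contact, so this is a possibility and not a certainty.

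**The case against.** The best defence is that Table 1 and the diet start date together already set an operative window. A patient booked 14 days out has no scheduled randomization point. Recruitment says patients are registered after consent but gives no date, and Table 1 supplies one. This largely stands: the window is implied. For long-wait patients, what remains is early approach, consent and perhaps baseline measurement, not mistimed treatment. The defence does not remove the conflict, because the numbered eligibility list does not carry the window and Recruitment sends staff to patients outside it. Condensation for publication is no answer either, since the list and the recruitment steps are printed in detail.

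A reader might infer several stronger points that the document does not support:

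- **That 59% fails the 80% benchmark.** The benchmark is a mean over the arm; 59% is a conditional ceiling for one patient.
- **That the recruitment target is in doubt.** The Sample size section calls its 480-640 patients a month only potentially eligible and applies none of the exclusions. Even if an arbitrary quarter of the lower figure were in window, 480 × 0.25 = 120 a month is 7.5 times the 16 needed.
- **That surgery would be moved to fit the diet.** Nothing in the text suggests this.
- **That sites could not be compared.** No between-site comparison of adherence is planned, recruitment is counted directly at each site, and randomization is stratified by center.

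**Conclusion.** The point holds as an inconsistency between sections, with consequences for how the primary feasibility outcomes are read. Trial population and Recruitment do not carry the window that the intervention section and Table 1 require, and no handling is stated for patients with fewer than 23 or more than 60 days between first contact and surgery. Here, being unable to receive the intervention means being unable to receive the full course as scheduled.

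The textual omission is certain; its practical size is not. The document gives no waiting times, so the 10-30% shares, the 80% agreement and the 90% adherence above are assumptions that show only direction and scale. Under them, the choice of denominator can decide whether the 70% randomization criterion is met, while the arm-mean adherence criterion is less sensitive. The correction is worth making because it is cheap and because these outcomes inform a definitive trial of 1158 patients.

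**What to change.** Reconcile Trial population, Recruitment, the intervention section and Table 1:

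1. Add an eligibility criterion that the booked surgery date leaves room for the full intervention period after randomization, whatever period the sponsor fixes. No particular window is proposed here.
2. In Recruitment, tie approach, consent and baseline measurement to a known surgery date within the Table 1 window, instead of to the first consultation alone.
3. In Feasibility outcomes, state whether patients found to be outside the window count as approached.
4. Settle the count of diet days against the supply (22 against 21), so that the prescribed-dose denominator is fixed.

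The cost is one eligibility line, a recruitment sentence and two clarifications of definitions. The downside is that somewhat fewer patients will be eligible.
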